## Abstract

**Background:**

Post-stroke lower limb spasticity (PSLLS) has a prevalence of 28–37%. PSLLS can cause difficulty in walking and reduce quality of life (QOL). Post stroke spasticity impairs the ability to intervene to improve walking ability. Botulinum Toxin A (BT) is an effective intervention for focal spasticity, but its use is currently restricted in many countries by their reimbursement system stating that the evidence for improvement in walking and quality of life (QOL) is not robust for treatment in the lower limb. This randomized control trial (RCT) will investigate the effectiveness of BT in modifying spasticity, and improving functioning (mobility, walking, activities of daily living (ADL’s) and QOL.

**Methods/design:**

A double-blind placebo-controlled trial injection will assess the effect of BT compared with a placebo (normal saline) in a sample of *n* = 94 patients. Following treatment of spasticity measured by Modified Ashworth Scale (MAS), the primary outcome of gait velocity will be measured by i) Gait Rite (Electronic Walkway); ii) walking by 2 Min Walk Test; iii) balance by Berg Balance Scale; mobility by iv) Timed Up and Go (TUG); v) lower limb function by ABILICO; vi) patient related goal by Goal Attainment Scale (GAS); vii) QOL by SF 12 (Rand version); viii) activities of daily living by the Functional Autonomy Measurement System (SMAF). There will be an associated health economic analysis.

**Discussion:**

The study methodology is based on our systematic review 2026 studies, which concluded the evidence for improving mobility following use of BT to reduce spasticity was not robust. The results of this study could establish the use of BT in improving gait and lower limb function in PSLLS. This study could provide the evidence needed for reimbursement schemes to consider and changes to its funding policy for BT in PSLLS.

**Trial registration:**

The trial is registered with the Australia New Zealand Clinical Trails Registry (ANZCTR)-ANZCTRN12617001603303. Registered 07/12/2017.

## Background

Stroke is a leading cause of death and the third most common cause of long-term adult disability in the developed world [1]. Stroke is Australia’s second biggest killer after coronary artery disease and a leading cause of disability. More than two thirds of stroke survivors develop impaired motor function and post-stroke spasticity. Post-stroke spasticity can significantly restrict stroke survivor’s mobility and functional ability, their activities of daily living and can diminish their quality of life. Motor impairments manifest as limitation of muscle control, body movements and associated functions, and typically affect one half of the body - the arm and the leg. The Stroke Foundation of Australia estimates there were 60,000 new and recurrent stroke cases in Australia in 2011 [2]. The cost of stroke burden is $2.14 billion a year. In recent decades, significant advances have taken place in diagnosis, management and prevention of stroke. However, stroke survivors continue to face great challenges due to long-term impairments and many lose their ability to live independently. Motor impairment is the most common and widely recognised impairment caused by stroke [3].

The prevalence of spasticity following stroke is between 17 and 46% [4]. Spasticity has been defined as “motor disorder characterized by velocity-dependent increase in tonic stretch reflexes (muscle tone) with exaggerated tendon jerks resulting from hyper excitability of the stretch reflex, as one component of the upper motor neuron syndrome.” [5, 6]. The effect of spasticity is profound. Following stroke, the body goes into safe mode (spasticity) causing loss of movement control, painful spasms, abnormal posture, increased muscle tone, and an overall decline in the function of muscles [7]. Langhammer [8], showed that post stroke motor impairments have a major impact on motor function, balance, gait, mobility, and activities of daily living, however, patients can improve with intensive exercise training [8]. The first problem to deal with, in achieving this, is the effects of spasticity (muscle stiffness) on muscle tone and flexibility. Spasticity interferes with or stops the exercise prescription. There is strong evidence that intensive exercise following a stroke can rewire the brain and has neuro-protective effects by activating specific neural circuits and increasing molecules that enhance synaptic plasticity [8]. Repetitive task specific exercise training will produce the behavioural experience, that is the most potent modulator of brain plasticity [9] and shown to improve outcomes such as balance, mobility, and in walking distance [8]. Post stroke exercise and motor re-education is therefore an important rehabilitation tool. There is, however good evidence that BT has clinical benefit in treating the mechanical effects of spasticity and in preparing the way for exercise training [10, 11]. The key to improving stroke outcomes is first; to deal with spasticity, then implement a structured exercise program and rehabilitation. This study will detail an intervention reducing lower limb spasticity followed by the structured exercise and rehabilitation program.

Our recent systematic review of 2026 studies of spasticity treatment, using BT in the lower limb, showed only five studies fitted our criteria of randomized controlled trials describing the efficacy of BT [12]. Even in these five studies there were major design problems including sample selection, study inclusion criteria, outcome measures, administration of BT, and methods of statistical analysis [13–17]. From the studies done to date on the lower limb, the evidence base for improvement of active functions such as gait velocity, walking distance and quality of life using BT for lower limb post stroke spasticity, is not robust.

The aims of this study is to investigate the primary outcome of gait velocity by Gait Rite (Electronic Walkway) and the secondary outcomes are measuring spasticity by Modified Ashworth Scale (MAS), walking by 2 Min Walk Test [18]; balance by Berg Balance Scale [19]; mobility by Timed Up and Go (TUG) [20]; lower limb function by ABILICO [21]; patient related goal by Goal Attainment Scale (GAS) [22]; QOL by SF 12 (Rand version); activities of daily living by the Functional Autonomy Measurement System (SMAF) [23].

## Methods and design

The study is a single center study based in Central Adelaide Local Health Network (CALHN) and operated out of 2 campuses: the Queen Elizabeth Hospital and the Hampstead Rehabilitation Centre. The design of the study is a double- blind, randomized, placebo-controlled trial (RCT) of one set of intramuscular injections of BT to the intervention group and one placebo to the control group.

### Participant recruitment and settings

Recruitment to the study will be through via referrals from.

1) Acute stroke units and stroke rehabilitation units of CALHN;

2) General practitioners; and.

3) Private specialists.

Recruitment will also be through promotional flyers distributed via the Stroke Foundation of South Australia.

### Ethics and trial registration

This trial has received the approval from the Hospital Research Ethics Committee (under Central Adelaide Local Health Network (Q20170509). The trial is registered with the Australia New Zealand Clinical Trails Registry (ANZCTR)-ANZCTRN12617001603303 [24].

### Inclusion criteria

Male or female subjects aged 20 to 80 years of age are eligible for this study if they have suffered a stroke resulting in focal spasticity in the knee causing stiff knee and/or equinovarus deformity, and have a Modified Ashworth Scale (MAS) of spasticity of 3+ in the quadriceps, Gastrocnemius/Soleus, Tibialis Posterior, Flexor Digitorum Longus, Flexor Hallucis Longus, or with any difficulty in weight bearing on the leg or walking with reduced speed of gait following stroke will be included. Note will be made of the first stroke and/or previous strokes. All patients should have been walking (with a stick or without any aid) normally prior to stroke.

### Exclusion criteria

Significant speech or cognitive impairmentSignificant lower limb problems such as fracture or arthritis, evidence of fixed contractureUse of BT type A in the previous six months, other non-stroke neurological disorders causing lower limb spasticitySignificant illness, such as malignancyContraindication to BT type APregnancy and lactationOsteoarthritic knee or hip having pain score of 3/10 or more on Visual Analog ScaleDepression with the score of > 12/15 on Geriatric Depression Scale (65 years+) and score of > 30/63 on Beck Depression Inventory (under 65 years)Individuals on antispasticity medications such as Baclofen, Tizanidine, Dantrolene and Diazepam.

### Consent and randomization

Once eligible for the study, the participants will be provided with information about the study. After obtaining the informed consent, they will be randomized to either the intervention or the control group by the hospital pharmacist external to this project. We will be looking at the imaging (CT/MRI) to determine the type of stroke (Ischaemic vs Haemorrhagic) and there will be stratification within stroke types utilizing block permutation design. Rights of withdrawal without prejudice to future treatment at any time in the study will be emphasized.

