### Procedures

Participants will undergo assessments at base line, 3 weeks, 3 months and 5 months following the injection (Fig. 1). All primary and secondary outcomes will be measured at all 4 time points. Additionally, the demographic and health characteristics such as age, gender, weight, type of stroke, affected side and mean time since stroke will he determined. A sensory evaluation will also be carried out in all the participants in the RCT.

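### Patients may enter at any time since stroke, yet neither the randomisation nor a fixed covariate accounts for it, so the gait-velocity comparison loses precision

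*Protocol article*

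**What the plan says.** Participant recruitment and settings lists "Acute stroke units and stroke rehabilitation units of CALHN", then general practitioners and private specialists, and adds: "Recruitment will also be through promotional flyers distributed via the Stroke Foundation of South Australia".

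Inclusion criteria begin: "Male or female subjects aged 20 to 80 years of age are eligible for this study if they have suffered a stroke". Neither the inclusion nor the exclusion criteria give a minimum or maximum time since that stroke. Prior botulinum toxin (BT) is excluded only if it was used within the last six months, so a patient treated before that may enter.

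Consent and randomization takes stroke type (ischaemic or haemorrhagic) from imaging and states that "there will be stratification within stroke types utilizing block permutation design". No other stratification factor is named.

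Procedures lists "type of stroke, affected side and mean time since stroke" among the characteristics to be collected, and sets "assessments at base line, 3 weeks, 3 months and 5 months following the injection". Outcomes makes change in gait velocity primary.

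Statistical methods plans a linear mixed effects model and names no covariates. Whether a baseline characteristic is adjusted for depends on whether the arms are seen to differ on it.

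**The concern.** The recruitment routes and the open eligibility allow one sample to hold patients soon after a stroke and patients long after one. The documents do not say that time since stroke predicts change in walking. That is a reasonable clinical expectation: recent patients may still be improving on their own while others are stable.

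If so, time since stroke explains part of the between-patient spread in the primary outcome, and the plan makes no firm use of it. Randomisation does not balance it. The analysis would use it only if an imbalance happened to be noticed. That rule has two weaknesses. It leaves the primary model to be settled after the baseline data are seen. It also recovers no precision when the arms look alike, although adjusting for a prognostic variable helps in that case too.

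At stake are a wider confidence interval and a single result that is easier to dispute, in a trial whose Discussion hopes to support a change in funding policy.

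**Working it through.** **1. The plan's own sample size.** Inputs from Sample size calculation: difference 0.13, SD 0.13, two-sided 5%, power 90%, design effect 1.5, attrition 25%.

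- Two-sample t-test at a standardised effect of 1: 22.02, so 23 per arm.
- 23 × 1.5 = 34.5, so 35.
- 35 / 0.75 = 46.7, so 47.

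The stated figures reproduce.

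**2. Effect of mixing recent and later strokes.** Let p be the share of recent strokes and r their extra spontaneous gain in gait velocity. Neither is in the documents. I take p = 0.2 to 0.5 and r = 0.1 to 0.3 m/s, read the protocol's 0.13 points as m/s, and assume that 0.13 is the SD within each group of patients. Then

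SD = √(0.13² + p(1−p)r²).

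- Central case, p = 0.3 and r = 0.2: added variance 0.3 × 0.7 × 0.04 = 0.0084, against 0.0169. SD = √0.0253 = 0.159, a variance increase of 50%.
- Lowest, p = 0.2 and r = 0.1: √(0.0169 + 0.0016) = 0.136 (+9%).
- Highest, p = 0.5 and r = 0.3: √(0.0169 + 0.0225) = 0.199 (+133%).

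**3. Power for a difference of 0.13 (two-sided t-test).**

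| SD | 23 per arm | 35 per arm | 47 per arm |
|---|---|---|---|
| 0.130 (as planned) | 91% | 98% | 99.8% |
| 0.136 (lowest) | 89% | 98% | 99.6% |
| 0.159 (central) | 77% | 92% | 97.5% |
| 0.199 (highest) | 58% | 77% | 88% |

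The 35 column is the expected number of completers with the design effect ignored. The 23 column applies if the full design effect of 1.5 is really needed.

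**4. Chance imbalance.** The 95% half-width of the difference between arms in the share of recent strokes is 1.96 × √(2p(1−p)/n). For p = 0.3 and n = 47 it is 1.96 × √(0.42/47) = 0.185, about 18.5 percentage points. Multiplied by r = 0.2 this is ±0.037 m/s. With 35 per arm and 21 recent strokes among the 70, an imbalance of 10 points or more arises by chance in about 30% of trials.

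**5. Steps 2 and 4 are one quantity.** At 47 per arm the 95% half-width of the treatment difference is 1.96 × 0.13 × √(2/47) = 0.053 with no mixing, and 1.96 × 0.159 × √(2/47) = 0.064 in the central case. Since √(0.053² + 0.037²) ≈ 0.064, the ±0.037 is the part that widens the interval. It is not a further error on top of it.

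**6. What adjustment recovers.** If the two-group picture holds and the model captures it, the residual SD returns to 0.13. In the central case, power at 35 per arm then goes from 92% back to 98%.

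**The case against.** A reader might infer that this trial cannot separate a BT effect from natural recovery. The documents do not support that. Recovery occurs in both randomised arms, and the double-blind placebo group is there to subtract it. Chance imbalance in one trial is ordinary sampling error. The estimate is unbiased on average, and a confidence interval using the observed SD already covers it.

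A reader might also infer that patients recruited from wards would have a different therapy background. Routine physiotherapy and standard care gives all participants the same frequency, duration and intensity, so the text does not support that either.

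Several further objections stand in part:

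- Power at 35 completers stays above the planned 90% across the assumed range unless the extra gain is 0.3 m/s, more than twice the target difference.
- The plan says only that its SD rests on available evidence. If that came from patients with mixed times since stroke, some or all of the added variance is already counted.
- Referral from an acute unit does not show that patients are injected soon after the stroke. The case mix is inferred from open eligibility.
- No visit is named as the primary time point. Spontaneous change by 3 weeks would be smaller than over 5 months.
- Stratifying on stroke type is a legitimate choice, and extra strata leave more incomplete blocks.

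The strongest objection is that the plan does provide for adjustment, and time since stroke is among the characteristics collected. A visible imbalance could therefore be dealt with, and a covariate list may normally sit in the SAP. But the article goes further than leaving the list open: it states a selection rule. That rule commits to no adjustment for time since stroke and gives up the precision gain when the arms look balanced. It softens the point without answering it.

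**Conclusion.** The point holds as one of precision and of how firmly the primary analysis is fixed. Eligibility is open on time since stroke, stroke type is the only stratum, and adjustment is contingent on observed differences.

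The size cannot be read from the documents. It depends on the case mix, on the extra recovery in recent strokes, and on whether 0.13 is an SD within similar patients. At the low end of the assumed range the loss is negligible. In the central case the confidence interval is about a fifth wider (0.064 against 0.053 at 47 per arm), and power at 35 completers remains about 92% with the design effect ignored. Only at the high end, or if the full design effect is needed, does power drop well below plan. Neither validity nor average unbiasedness is in question. The case for acting is that the remedy is almost free.

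**What to change.** In Statistical methods, replace the selection of covariates by observed baseline differences with a fixed list for the primary mixed model: time since stroke, its interaction with visit, and the stratification factor stroke type. The interaction matters because spontaneous recovery acts on change over time. A main effect alone would shift all visits equally. Fix the form of time since stroke in advance, either continuous or two levels with a cut chosen before unblinding. This costs a few lines of text and a handful of model parameters. The variable is already listed under Procedures; it should be recorded per patient.

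Optionally, if randomisation has not begun, add a two-level time-since-stroke stratum to the pharmacy's permuted-block list. Crossed with stroke type this gives four strata for 94 patients. The downside is a few incomplete blocks, probably in the smaller strata. The covariate adjustment is worth making whether or not the stratum is added.

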### Outcomes

Primary outcome include change inGait velocity/walking distance in GaitRite (Electronic walkway)

Secondary outcomes include changes inSpasticity measured by Modified Ashworth Scale (MAS)2 Min Walk Test [18]Berg Balance Score [19]Timed Up and Go (TUG) [20]Lower limb function by ABILICO [21]Goal Attainment Scale (GAS) [22]Quality of life by SF 12 (Rand version)ADL score -The Functional Autonomy Measurement System (SMAF) [23]Passive range of motion at the ankle joint.Use of ActivPAL to quantify ambulatory activities at home [25]

### Procedures

Participants will undergo assessments at base line, 3 weeks, 3 months and 5 months following the injection (Fig. 1). All primary and secondary outcomes will be measured at all 4 time points. Additionally, the demographic and health characteristics such as age, gender, weight, type of stroke, affected side and mean time since stroke will he determined. A sensory evaluation will also be carried out in all the participants in the RCT.

**Fig. 1 Fig1:**
[figure not shown]
Study Design- Randomized Controlled Trial

We will also conduct a qualitative study described below. Both groups will receive standardized physiotherapy, including intensive exercise training, in terms of frequency, intensity and duration [8].

### BT and placebo administration to intervention and control

All treatment be it intervention or placebo (saline) will be constituted to the same type of syringes by the independent pharmacist. For all patients, physician will prescribe a dose of BT to be injected but will not be aware whether the syringe contains the active drug or placebo.

The intervention group will receive a targeted BT injection (up to 400 units of BT, Allergan, 1 vial will be reconstituted with 2 ml of normal saline) into the lower limb spastic muscles. The spastic muscles will be identified clinically and confirmed by EMG, (DANTEC CLAVIS). Maximum dose of Botox per session is 400 units (approved by TGA). The dose is dependent on the number of muscles and the size of the muscle involved. The most common deformity in post-stroke patients is equinovarus deformity. In an equinovarus deformity (caused by Gastrocnemius/soleus, Tibialis Posterior) the implicated muscles may require the following dosages. Gastrocnemius/Soleus-causing equinus deformity (plantarflexion)- may need up to 300 units. Tibialis Posterior – causing equinus and varus deformity- may need up to 200 units. Flexor Pollicis Longus and Flexor Digitorum Longus (causing clawing of great toe and other toes) - may need 100–150 units each. Patient specific dosage will be identified by the study physician at the start of the trial.

The pharmacist involved in randomization will constitute the dose into the same volume. The study physician will prescribe the dose but will get the same volume each time and won’t know if it is active or not. The Queen Elizabeth Hospital Pharmacy department will handle the medications and will prepare the identical looking blinded syringes.

### Routine physiotherapy and standard care

All participants in the study will receive physiotherapy and standard care such as orthotics (both in the intervention and the control group). This will include stretching, balancing, strengthening exercises and gait retraining. Gait retraining (task specific) will include walking on the level ground and then progressing to walking on inclines and different surfaces. Therapy will be standardized in terms of frequency (two sessions/week in the Physiotherapy department at the Queen Elizabeth Hospital, duration (45 min each session) and intensity (4–6 in Borg’s Scale of Perceived Exertion i.e. somewhat hard and hard). Patients will also be given a home exercise program. Compliance will be recorded monthly where participant activity will be recorded through phone calls. Additionally, phone calls will be made to encourage and motivate participants whereby they will be given advice about diet, weight and activity management. Activity at home will be monitored by ActivPal in sample subjects.

### Withdrawal criteria

Withdrawal criteria will cover subjects unable to comply with the study protocol, for any reason, or lost to follow up after 3 attempts of contact.

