### Sample size calculation

In most of the RCT’s included in our systematic review sample inadequacies were identified. Chief among these was the problem of inadequate sample calculations for repeated measures design. In repeated measures studies, within patient observations are correlated which often results in an estimate of the standard deviation that is an underestimate of the true standard deviation. Failure to account for this leads to an increased in the risk of a Type 1 error. In this study, we inflated our sample size by applying a design effect (DEFF) of 1.5 to account for the repeated measure design. Calculations were based on the requirement that effects be detected at the 5% alpha level with 90% statistical power. Based on available evidence, it was assumed that the clinically meaningful difference between the two treatment groups would be 0.13 points in gait speed with a standard deviation of 0.13. Based on these assumptions, a sample of 35 patients per group is required following the application of the design effect (*n* = 23 * DEFF). We have further inflated the sample size to *n* = 47 per group to account for an expected attrition rate of 25%.

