### Statistical methods

An intention-to-treat (ITT) and per-protocol analysis is planned. The data will be summarized using means with standard deviations and medians with inter-quartile range. Counts and percentages will be used to describe categorical measures. Baseline characteristics will be assessed to identify any differences between treatment groups that would require adjustment in subsequent analyses. A linear mixed effects model will be applied to assess treatment effects over time. Pairwise, post hoc comparisons will be made using the Student t-test. All tests will be two-tailed and assessed at the 5% alpha level.

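### The withdrawal rule makes non-compliance a ground for leaving the study and does not separate stopping therapy from stopping assessment, which undermines the intention-to-treat analysis

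*Protocol article*

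**What the plan says.** The whole rule is one sentence in the section on withdrawal of the protocol article. It opens: "Withdrawal criteria will cover subjects unable to comply with the study protocol, for any reason". The same sentence then adds participants who cannot be reached in three tries. Non-compliance and loss to follow-up stand side by side as grounds for withdrawal.

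Four other sections bear on it:

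- **Methods and design:** the randomised treatment is "one set of intramuscular injections of BT to the intervention group and one placebo to the control group".
- **Procedures:** all primary and secondary outcomes are measured at baseline, 3 weeks, 3 months and 5 months. Routine physiotherapy and standard care adds two 45-minute hospital sessions a week, a home programme, and monthly recording of compliance by telephone.
- **Statistical methods:** "An intention-to-treat (ITT) and per-protocol analysis is planned". The model is given as "A linear mixed effects model will be applied to assess treatment effects over time", followed by pairwise Student t-tests.
- **Sample size calculation:** the group size is raised from 35 to 47 "to account for an expected attrition rate of 25" per cent.

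The article does not say that withdrawn participants continue to be assessed. It also does not say that they leave the ITT set or that their data are discarded.

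**The concern.** Once the injections have been given, no later dose can be missed. A participant can then fail to comply only by missing physiotherapy, home exercise, calls or assessment visits. Someone who has given up physiotherapy can still walk over the electronic walkway at 3 months. A rule that withdraws that person from the study, in the usual sense of the word, loses an outcome that was there to be measured.

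The loss need not be neutral. Compliance arises after randomisation. The Background says that spasticity obstructs exercise, so if the toxin works, placebo participants may find the programme harder to keep up. Conversely, transient weakness, listed under Adverse events, could reduce compliance on active treatment. The direction is uncertain, but balance between arms cannot be assumed.

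The ITT and per-protocol analyses differ in how they treat non-compliers. If non-compliers stop being measured, the ITT analysis lacks their later outcomes and moves towards the per-protocol one.

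**Working it through.** **1. The plan's own figure.** Inputs from Sample size calculation and Statistical methods: difference 0.13, SD 0.13, two-sided 5% alpha, 90% power, design effect 1.5, attrition 25%.

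- Normal approximation: n = 2 × (z for alpha + z for power)² × (SD/difference)² = 21.01, rounded up to 22 per group.
- t-test solution: 22.02, rounded up to 23, as stated.
- 23 × 1.5 = 34.5, rounded to 35. Then 35 / 0.75 = 46.7, rounded to 47. Total 2 × 47 = 94.

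The stated size reproduces, and 25% loss (0.25 × 47 = 11.75, about 12 per group) is already allowed for.

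**2. Is it a power problem?** Power of a t-test at standardised effect 1.0, with effective size = observed number / 1.5:

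| Observed per group | Missing | Power |
|---|---|---|
| 47 | 0% | 97% |
| 35 | 26% | 92% |
| 30 | 36% | 87% |
| 25 | 47% | 80% |

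Power falls below 90% only when losses exceed about 30% (33 observed per group gives 90.0%). The issue is bias, not power.

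**3. Size of bias in an observed-case comparison.** The article gives no withdrawal rates by arm and no outcome difference between those withdrawn and those retained, so these are assumptions. Let p be the proportion withdrawn in an arm, and D the amount by which those withdrawn would have walked more slowly than those retained. The mean of the retained is then the arm mean plus p × D, and the treatment difference shifts by (p active − p placebo) × D.

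- 25% and 25%: shift 0 for any common D.
- 20% active, 30% placebo: −0.10 × 0.13 = −0.013; −0.10 × 0.26 = −0.026.
- 15% active, 35% placebo: −0.20 × 0.13 = −0.026; −0.20 × 0.26 = −0.052, which is 20% to 40% of the 0.13 target.
- 35% active, 15% placebo: the same sizes with the opposite sign (+0.026 to +0.052), which would inflate the effect.

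**4. What the planned mixed model does.** Simulation with 400,000 per arm, SD 0.13, true difference 0.13 and 25% overall loss. Dropout is logistic in 3-week velocity (slopes −0.5 to −1.5 per SD), and the correlation of 3-week with later velocity is 0.7 or 0.85 (all assumed). Losses are 29–35% on placebo and 15–21% on active.

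| Estimate | Treatment difference (true 0.130) |
|---|---|
| Retained participants only | 0.107 to 0.127 |
| Likelihood estimate using the 3-week value | 0.129 to 0.130 |

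So when dropout depends only on values already observed, the bias almost disappears under the planned model.

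**5. What the model does not repair.** A participant withdrawn before 3 weeks contributes a baseline value and nothing about response. If such withdrawal, or any later one, follows a decline that no visit recorded, the missing-at-random condition fails. The pairwise t-tests in Statistical methods use observed cases only, so the shifts in step 3 apply to them directly.

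**The case against.** The best defence has four parts.

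- **The mixed model.** The planned primary model handles the most natural form of dropout, as step 4 shows. This stands for dropout on observed values and sets aside the completers' figures as a description of the model's estimate. It does not cover early or unobserved-decline withdrawal, or the t-tests.
- **Withdrawal is not exclusion from ITT.** A reader might infer that the rule contradicts the ITT analysis and removes non-compliers from it. The document does not support that. It nowhere drops withdrawn participants from the ITT set or discards their data, and a mixed model can use whatever they contributed. The end of assessment is the ordinary reading of study withdrawal, not something the article states.
- **The text says unable to comply.** No attendance threshold is set, and the monthly calls are there partly to motivate. That is fair: missing one session or call is not stated to trigger withdrawal. But the phrase covering any reason leaves no limit either, and compliance is logged monthly, so there is a ready trigger. The three-attempts clause is an ordinary definition of loss to follow-up and is not at fault.
- **Detail may sit elsewhere.** Follow-up after withdrawal and the ranking of the two analysis sets are commonly left to the full protocol or the SAP, and their absence here is no criticism. What is criticised is the rule that the article does state. If applied at the clinic, it produces missing outcomes that no later analysis plan can recover.

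**Conclusion.** The point holds as a weakness in a stated rule, at should-fix level. It makes non-compliance a ground for study withdrawal without separating therapy from assessment. In a trial with one injection session, its ordinary reading loses measurable gait outcomes, possibly selectively, and so undermines the ITT analysis.

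The size depends on assumptions. It is nil in an observed-case comparison if withdrawal is equal and equally related to outcome in both arms. It is close to nil in the mixed model if withdrawal depends only on recorded values. Under the unequal scenarios above, it is 0.013 to 0.052 in an observed-case difference. The sign is not determined by the document. A reader might also infer a shortage of power or a wrong sample size. Neither follows, because the 25% attrition is correctly budgeted and no stated figure changes.

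**What to change.** Reword Withdrawal criteria along these lines:

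- Non-adherence to physiotherapy, home exercise or calls is not by itself a reason to end follow-up.
- Study withdrawal is limited to withdrawn consent for follow-up, or true loss to follow-up. The existing three-attempts definition can stay.
- All randomised participants are invited to the 3-week, 3-month and 5-month assessments, whatever their adherence.
- Non-compliance is dealt with in the definition of the per-protocol set.

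This concerns outcome collection only and changes no treatment, dose or sample size. The cost is a wording amendment and some extra effort to bring non-adherent participants to visits already planned. It should be made before follow-up starts, because outcomes not collected cannot be restored afterwards.
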